## Abstract

**Background:**

Globally, head and neck squamous cell carcinoma (HNSCC) is the seventh most common malignancy. Despite aggressive multimodal treatment approaches, recurrent and/or metastatic (R/M) disease develops in >50% of patients. In this setting, pembrolizumab was approved for patients with PD-L1 expression. However, response rates with checkpoint inhibitor monotherapy remain limited and strategies to strengthen tumor-directed immune responses are needed.

**Objective:**

The FOCUS trial is designed to estimate the effectiveness of UV1 vaccination in combination with pembrolizumab versus pembrolizumab as a single agent in patients with R/M HNSCC.

**Methods and analysis:**

The FOCUS trial is a two-armed, randomized, multicenter phase II study which was designed to evaluate the efficacy and feasibility of the hTERT-targeted cancer vaccine UV1 as add-on to pembrolizumab in the 1st line treatment of patients with R/M PD-L1 positive (combined positive score ≥1) HNSCC. Secondary objectives are the exploration of patient subgroups most likely deriving benefit from this novel combination and the establishment of liquid biopsy tumor monitoring in HNSCC.

**Ethics and dissemination:**

This clinical study was designed and will be conducted in compliance with Good Clinical Practice and in accordance with the Declaration of Helsinki. It is intended to publish the results of this study in peer-reviewed scientific journals and to present its content at academic conferences.

**Conclusions:**

A significant number of patients with R/M HNSCC are frail and may not tolerate chemotherapy, these patients may only be suitable for pembrolizumab monotherapy. However, long term disease stabilizations remain the exception and there is a need for the development of efficacious combination regimens for this patient population. The FOCUS study aims to optimize treatment of R/M HNSCC patients with this promising new treatment approach.

**Clinical Trial Registration:**

https://clinicaltrials.gov/study/NCT05075122, identifier NCT05075122.

## Introduction

1

Worldwide, head and neck squamous cell carcinoma (HNSCC) is the seventh most common malignancy with more than 660,000 new cases and 350,000 deaths per year (1). Risk factors include tobacco use, alcohol consumption, and human papilloma virus (HPV) infection (2).

At early stages, therapy is given with curative intent. However, despite aggressive treatment with multimodal approaches, recurrent and/or metastatic (R/M) disease develops in more than half of patients with HNSCC and prognosis of these patients is poor (3). Many patients suffering from R/M disease present with unresectable disease and only qualify for palliative treatment (4). Until 2019, the EXTREME regimen (cetuximab combined with platinum and fluorouracil) was the standard of care first line treatment for patients with R/M HNSCC with good performance status (ECOG 0-1) (5). More recently, pembrolizumab was approved for R/M HNSCC as monotherapy or in combination with platinum-fluorouracil for PD-L1 positive disease. Approval was based on the KEYNOTE-048 trial, a randomized, phase 3 study, which showed a significant survival benefit when compared with the EXTREME protocol (6). In this trial, pembrolizumab plus chemotherapy improved overall survival compared to cetuximab plus chemotherapy (median 13.0 *vs*. 10.7 months, HR 0.77 [95% CI 0.63-0.93], p=0.0034). In the subgroups of patients with PD-L1 CPS ≥1 and CPS of ≥20, pembrolizumab given as a single agent improved overall survival compared to cetuximab plus chemotherapy (12.3 *vs*. 10.3 months, HR 0.78 [95% CI 0.64-0.96], p=0.0086, and 14.9 *vs*. 10.7 months, HR 0.61 [95% CI 0.45-0.83], p=0.0007) demonstrating increased efficacy of pembrolizumab with increasing PD-L1 expression (7).

Although some patients have durable responses to immune-checkpoint inhibitors, many patients with R/M HNSCC either show no response or benefit only in the short-term from this treatment (3). One reason might be an insufficient T cell effector response (8). To improve the T cell response against tumor antigens, therapeutic cancer vaccines in combination with immune-checkpoint inhibitors are investigated in HNSCC and other tumor entities (8, 9). UV1 is a peptide vaccine targeting human telomerase reverse transcriptase (hTERT), found to be activated in 85-90% of all cancers (8) representing an essential step in carcinogenesis (10). The UV1 vaccine induced persistent immune responses which lasted up to 7.5 years in phase I clinical trials which included patients with non-small cell lung cancer, malignant melanoma, and prostate cancer (8). When combined with the checkpoint-inhibitor ipilimumab, the vaccine-induced T cell response in the melanoma trial occurred more often and more rapidly indicating improved efficacy with the combined approach (8). In patients with advanced melanoma, UV1 was also combined with pembrolizumab (11). In this phase I clinical trial, treatment was well tolerated and response rate was 60% with a 1-year survival rate of 85% (11).

In patients with HNSCC, the combination of immune-checkpoint inhibition with UV1 has not been studied. In 75-100% of HNSCC high levels of hTERT expression have been detected (12). The most common mechanism of hTERT activation are mutations in the promoter region of hTERT (13). In HNSCC frequencies of hTERT promoter mutations vary among different studies (14). Frequencies up to 64,7% have been reported depending on tumor site, risk factors such as human papillomavirus status and ethnicity (14). Thus, hTERT represents an attractive target for therapeutic vaccination in HNSCC.

The FOCUS trial was designed to estimate the effectiveness of UV1 vaccination in combination with pembrolizumab versus pembrolizumab as a single agent in patients with R/M HNSCC.

## Methods and analysis

2

### Study objective

2.1

The primary objective of this study is to assess the efficacy of UV1 vaccination in combination with pembrolizumab in patients with R/M HNSCC and PD-L1 CPS ≥1 based on progression free survival according to iRECIST (progression-free survival rate at 6 months after randomization, PFS@6) (15).

Secondary clinical endpoints of this study are overall survival, objective response rate and duration of response according to iRECIST. Other secondary objectives are the UV1 vaccine induced immune responses and the clearance rate of ctDNA from blood during treatment. Additionally, this study will explore the safety and tolerability of UV1 vaccination in combination with pembrolizumab according to NCI CTCAE v5.0. Other objectives are the exploration of what patient subgroups benefit most from this combined approach and the establishment of liquid biopsy tumor monitoring in HNSCC.

### Study design

2.2

The FOCUS trial is an open-label, randomized, phase II study which investigates the tolerability and efficacy of the UV1 vaccine in patients with R/M PD-L1 positive (CPS ≥1) HNSCC planned for first-line treatment with pembrolizumab. The study is multicentric and includes several study sites in Germany. 75 patients will be randomized with an estimated recruitment phase of 24 months. Planned duration of follow-up per patient is until death or 12 months after last patient in (**Figure 1**).

**Figure 1 f1:**
[figure not shown]
Study recruitment and follow-up. FPFV, first patient, first visit; LPFV, last patient, first visit; LPLV, last patient, last visit.

### Treatment

2.3

Eligible patients (**Table 1**) will be randomized to either pembrolizumab, Arm A, about 25 patients, or pembrolizumab in combination with UV1 vaccination plus sargramostim (GM-CSF) as an adjuvant, Arm B, about 50 patients (**Figure 2**).

**Table 1 T1:** 

Inclusion criteria
• Males and Females who are at least 18 years of age • Histologically confirmed diagnosis of a non-resectable recurrent or metastatic head and neck squamous cell carcinoma (not necessarily reconfirmed at time of enrolment) • At least one measurable tumor lesion as per RECIST v1.1, (scan not older than 4 weeks before randomization) • Eligible for pembrolizumab monotherapy (PD-L1 CPS ≥1 and adequate laboratory parameters for pembrolizumab monotherapy as assessed by the investigator) • ECOG-performance score 0-2 • Written informed consent obtained according to international guidelines and local laws • Ability to understand and give informed consent • Safe contraception measures for males and females. Procedures with a pearl index of less than 1% apply as safe pregnancy prevention measures

**Figure 2 f2:**
[figure not shown]
Study schedule.

All patients will receive pembrolizumab until disease progression and up to two years in both arms.

The UV1 vaccine (Ultimovacs, Oslo, Norway) and sargramostim are considered investigational medical products (IMPs) in this study.

Data on efficacy in in terms of vaccine-specific immune response and safety from completed phase I/II clinical trials support a total of 8 vaccinations with a UV1 dose of 300µg administered intradermally with 75µg of the adjuvant sargramostim (8). The administration regimen for UV1 vaccination during day 1-10 is optimized for effective priming and expansion of naïve hTERT-specific T cells in the local lymph nodes draining the vaccine injection site. The following vaccinations are optimized for re-activation of T cell effector activity in the tumor microenvironment in synergy with pembrolizumab.

*Arm A:*

Patients in arm A receive pembrolizumab at 200mg flat dose iv every 3 weeks. Administration starts at week 1 (one week earlier than arm B). The duration of treatment will be 12 weeks.

*Arm B:*

Patients in arm B receive pembrolizumab at 200mg iv every 3 weeks in combination with UV1 vaccination (300µg UV1 plus 75µg GM-CSF as adjuvant). Three UV1 vaccinations are applied during the week before initiation of pembrolizumab, followed by 5 vaccinations applied every 3 weeks on d1 of each cycle (5 cycles in total). Administration of pembrolizumab starts at week 2. In total, the duration of treatment will be 13 weeks.

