**Table 2 T2:** 

Baseline assessment
• Informed consent • Review of inclusion and exclusion criteria • Relevant medical history • Laboratory tests: Hematology panel, chemistry panel, including also TSH, fT3/fT4, PT/PTT, INR/Quick • Hepatitis B/C screening test, HIV screening test (not older than 4 weeks before randomization) • Physical examination • Vital signs and ECOG • Radiological imaging by computertomography of the neck, chest, abdomen and pelvis (according to RECIST v1.1, not older than 4 weeks before randomization) • Urine pregnancy test • Concomitant medication • C-lab: Stored tumor tissue collection (paraffin block or 10 slides), remaining tumor tissue from the first diagnosis or at relapse • C-lab: Fecal sample

Assessments during treatment will be done on visit 1 (week 1 [W1] day 1 [D1]), visit 2 [W1 D3], visit 3 [W1 D5], visit 4 [W2], visit 5 [W5], visit 6 [W8], visit 7 [W11], visit 8 [W14] and end of treatment (EOT) according to **Table 3**. Screening and visit 1 can be performed on the same day. Assessments at progressive disease (PD) during treatment (if applicable) will be performed according to **Table 4**.

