**Table 3 T3:** 

Assessments during treatment
• Vital signs and ECOG (only for visit 1, 4, 5, 6, 7, 8 and EOT) • Laboratory tests: Hematology panel, chemistry panel (only for visits 1, 4, 5, 6, 7 and 8) • TSH, fT3/fT4 at visits 4, 5, 6, 7, 8 and EOT • Urine pregnancy test at visits 5, 6 and 7 • C-lab blood sampling (20ml) for tumor-DNA (only at visits 1, 5, 6, 8 and EOT) • On site preparation and storage: blood sampling (50ml) for PBMC, arm B only (for both arms at site 01 Halle) at visits 1 and 6 • Pembolizumab infusion (arm A) every 3 weeks according to the label at Visits 4, 5, 6, 7 and EOT (Visit 8) • Additional UV1 vaccination (arm B) 3 times the week before initiation of pembrolizumab followed by 5 additional applications on d1 cycle 1-5. • Adverse events • Concomitant medication • Radiological response (according to iRECIST) will be assessed at visit 8 (routine diagnostics)

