### Follow-up

2.5

All patients will be evaluated every 3 months after EOT until death or maximal 12 months after last patient in (**Table 5**). At progressive disease during follow-up (if not progressed during treatment), assessments will be done according to **Table 6**. All patients will be monitored 30 days after EOT for safety reasons (**Table 7**).

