**Table 5 T5:** 

Follow-up
• Results of Radiological imaging (according to iRECIST) regarding disease status (from routine diagnostics) until PD • Pembrolizumab infusion is continued according to SmPC at the discretion of the physician • C-lab blood sampling (20ml) for tumor-DNA (only at FU1 and FU2) • Assessment of adverse events, concomitant therapies (only until FU1), subsequent anti-cancer therapies and survival status

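### Arm A's pembrolizumab start and end of treatment are given two incompatible ways, and one of them moves the evaluation nearest month 6 a week earlier than in arm B

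*Protocol article*

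**What the plan says.** All places are in the protocol article.

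- Section 2.3, arm A: "Administration starts at week 1 (one week earlier than arm B). The duration of treatment will be 12 weeks". Dosing is every three weeks.
- Section 2.3, arm B: "Administration of pembrolizumab starts at week 2. In total, the duration of treatment will be 13 weeks".
- Section 2.4 gives one visit list, not split by arm: "visit 4 [W2], visit 5 [W5], visit 6 [W8], visit 7 [W11], visit 8 [W14] and end of treatment (EOT". It also states: "Screening and visit 1 can be performed on the same day".
- Table 3 lists arm A's pembrolizumab "infusion (arm A) every 3 weeks according to the label at Visits 4, 5, 6, 7 and EOT (Visit 8" and names no arm A infusion at Visit 1. It places the on-treatment radiological assessment at Visit 8, from routine diagnostics.
- Section 2.5: "All patients will be evaluated every 3 months after EOT until death or maximal 12 months after last patient in". Table 5 collects "Results of Radiological imaging (according to iRECIST) regarding disease status (from routine diagnostics) until PD".
- Section 2.1 defines the primary endpoint as "progression-free survival rate at 6 months after randomization, PFS@6".
- Section 2.8 makes arm A a calibration arm without a formal test between arms, and lets its findings contribute to the decision on further development.

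**The concern.** A site cannot tell from the text whether arm A's first infusion belongs in week 1 or week 2. Section 2.3 places it a week before arm B's. Table 3 places it in the same week as arm B's.

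The ambiguity extends beyond dosing because two clocks are in use. Follow-up visits are counted from EOT and the primary endpoint from randomization. If arm A finishes a week earlier, its first follow-up evaluation (FU1) also comes a week earlier, and FU1 is the scheduled evaluation closest to the six-month landmark. Disease status near the landmark could then be ascertained at different times in the two arms. What is at stake is the informal reading of arm B beside arm A.

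**Working it through.** **1. The two calendars.** Take Visit 1 (week 1, day 1) as day 0, so week *k* starts on day 7(*k* − 1).

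| | Infusion weeks | EOT |
|---|---|---|
| Arm A, section 2.3 | 1, 4, 7, 10, 13 | day 84 (12 weeks) |
| Arm A, Table 3 with visit list | 2, 5, 8, 11, 14 | day 91 |
| Arm B, section 2.3 and visit list | 2, 5, 8, 11, 14 | day 91 (13 weeks) |

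Arm B's stated 13 weeks is reproduced and agrees with the visit list. For arm A, the stated 12 weeks fits a week 1 start and EOT at week 13. It would also fit weeks 2 to 14 if counted from the first infusion, so the start week is what settles the conflict. Four of the five infusion weeks implied by section 2.3 (4, 7, 10 and 13) are not in the visit list.

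**2. Where FU1 falls.** Three months = 365.25/4 = 91.3 days; six months = 182.6 days = 26.09 weeks.

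- Arm A, section 2.3: 84 + 91.3 = 175.3 days = 25.04 weeks.
- Arm B: 91 + 91.3 = 182.3 days = 26.04 weeks.
- Arm A, Table 3: 182.3 days, the same as arm B.

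The next evaluation is at about 38 to 39 weeks, so FU1 is the nearest one in both arms. An equal lag from randomization to Visit 1 leaves the 7-day difference unchanged.

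**3. What a 7-day difference could do.** Assume the section 2.3 schedule and equal exponential PFS in both arms, S(t) = 0.25^(t/182.6), using the article's 25% control rate. Let *f* be the share of progressions seen only at a study evaluation; it is unknown. Take two ways of reading status at month 6:

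- *Confirmation*: a patient counts as progression-free only if an evaluation at or after the landmark shows it. Rate = (1 − f) × 0.25 + f × S(first evaluation at or after the landmark).
- *Scan date*: progression is dated to the scan that shows it. Rate = (1 − f) × 0.25 + f × S(last evaluation before the landmark).

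Example on exact dates, with *f* = 0.3 and Visit 1 three days after randomization:

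- Arm A's FU1 is at day 178.3, before the landmark; arm B's is at day 185.3, after it.
- Confirmation: arm A waits for its second follow-up at 84 + 182.6 + 3 = 269.6 days. Gap B − A = 0.3 × (0.2450 − 0.1292) = 3.5 points.
- Scan date: arm A's last evaluation before the landmark is FU1, and arm B's is EOT at day 94. Gap = 0.3 × (0.4899 − 0.2583) = 6.9 points.

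Exact dates are the extreme case. With each evaluation scattered uniformly (400,000 simulated draws; lags of 0, 3 and 7 days; both rules; *f* = 0.3):

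| Scatter of scan dates (assumed) | Gap B − A, points |
|---|---|
| ±7 days | 1.5 to 3.3 |
| ±14 days | 0.6 to 1.4 |
| ±28 days | 0.2 to 0.4 |

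The gap is proportional to *f*. At ±7 days it is 0.5 to 1.1 points for *f* = 0.1 and 2.5 to 5.5 for *f* = 0.5. At ±28 days and *f* = 0.1 it is about 0.1.

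**4. The sign.** On exact dates at *f* = 0.3 the gap reverses to −0.2 to −0.4 points at zero lag and −0.4 to −0.8 at a lag of 8 days, because FU1 then lies on the same side of the landmark in both arms. Zero lag is possible, since screening and Visit 1 may share a day. If status at FU1 is simply taken as status at month 6 and all status comes from that visit, arm A reads 0.25^(175.3/182.6) = 26.4% and arm B 25.1%. That is about 1.4 points in arm A's favour.

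**5. What does not move.** Arm B's EOT and FU1 are the same under both calendars. The 46 evaluable patients in section 2.9 are reproduced by an exact one-arm binomial rule: success at 16 or more of 46 gives alpha 0.0896 at 25% and power 0.808 at 40%. For scale, arm A's 95% half-width with 25 patients is 1.96 × √(0.25 × 0.75/25) = 17.0 points, and the planned gain is 40 − 25 = 15 points.

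**The case against.** The strongest reply is that follow-up visits collect the results of routine imaging, and nothing says that scans are ordered at EOT plus three months. Pembrolizumab continues after EOT, so EOT need not set the imaging rhythm. If scans run on their own timetable, assessment time does not depend on arm. This stands as a limit: the distortion is conditional on scans following the visits, and it shrinks quickly as scan dates spread.

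It is also fair that the primary inference compares arm B with a fixed 25%, that no test between arms is planned, and that any effect is well inside arm A's sampling error. All of that stands.

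A reader might infer that the schedule biases the trial in favour of arm B. The documents do not support this. The direction depends on the lag from randomization to Visit 1 and on how status at month 6 is read, and the article gives neither in enough detail to settle it.

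Finally, the study schedule figure is not shown and may label weeks by arm; the visit weeks may be meant for arm B only. The text and Table 3 do not say so, and Table 3 names arm A explicitly when it assigns infusions to Visits 4 to 8. If arm B only is the intention, the one-week offset of section 2.3 remains.

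**Conclusion.** The inconsistency is real and lies in the current text: arm A cannot both start in week 1, a week before arm B, and receive its infusions at the listed Visits 4 to 8. Under section 2.3 the scheduled evaluation nearest month 6 comes one week earlier in arm A; under Table 3 the shift is zero.

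The consequence for the calibration arm is possible but small and uncertain. At *f* = 0.3 it runs from 0.2–0.4 points (±28 days) to 1.5–3.3 points (±7 days). These figures rest on assumed values for *f*, the lag and the scatter, on exponential PFS, and on routine scans being tied to the visits. It would be going too far to conclude that the primary result is compromised. This is a minor point, worth correcting because the arm-dependent timing sits next to the primary landmark and is easy to avoid.

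**What to change.** State one start week and one EOT week for arm A, and make section 2.3, the visit list and Table 3 agree. If week 1 is intended, print arm A's own visit weeks (1, 4, 7, 10, 13). If week 2 is intended, correct section 2.3.

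In either case, time the two tumour evaluations already planned from randomization in both arms, at about weeks 13 and 26 with a window (for example ±7 days). The same timing in both arms removes the between-arm shift whichever way status at month 6 is read.

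The cost is wording in sections 2.3, 2.4 and 2.5 and Table 3, plus one operational demand: sites must request routine imaging within the window, about a week from its present timing in arm A under section 2.3. No patients and no evaluations are added.

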### Assessments

2.4

Baseline assessment is performed according to **Table 2**. Radiological imaging by computed tomography (CT) of the neck, chest, abdomen and pelvis according to RECIST v1.1 should not be older than 4 weeks before randomization.

**Table 2 T2:** 

Baseline assessment
• Informed consent • Review of inclusion and exclusion criteria • Relevant medical history • Laboratory tests: Hematology panel, chemistry panel, including also TSH, fT3/fT4, PT/PTT, INR/Quick • Hepatitis B/C screening test, HIV screening test (not older than 4 weeks before randomization) • Physical examination • Vital signs and ECOG • Radiological imaging by computertomography of the neck, chest, abdomen and pelvis (according to RECIST v1.1, not older than 4 weeks before randomization) • Urine pregnancy test • Concomitant medication • C-lab: Stored tumor tissue collection (paraffin block or 10 slides), remaining tumor tissue from the first diagnosis or at relapse • C-lab: Fecal sample

Assessments during treatment will be done on visit 1 (week 1 [W1] day 1 [D1]), visit 2 [W1 D3], visit 3 [W1 D5], visit 4 [W2], visit 5 [W5], visit 6 [W8], visit 7 [W11], visit 8 [W14] and end of treatment (EOT) according to **Table 3**. Screening and visit 1 can be performed on the same day. Assessments at progressive disease (PD) during treatment (if applicable) will be performed according to **Table 4**.

**Table 3 T3:** 

Assessments during treatment
• Vital signs and ECOG (only for visit 1, 4, 5, 6, 7, 8 and EOT) • Laboratory tests: Hematology panel, chemistry panel (only for visits 1, 4, 5, 6, 7 and 8) • TSH, fT3/fT4 at visits 4, 5, 6, 7, 8 and EOT • Urine pregnancy test at visits 5, 6 and 7 • C-lab blood sampling (20ml) for tumor-DNA (only at visits 1, 5, 6, 8 and EOT) • On site preparation and storage: blood sampling (50ml) for PBMC, arm B only (for both arms at site 01 Halle) at visits 1 and 6 • Pembolizumab infusion (arm A) every 3 weeks according to the label at Visits 4, 5, 6, 7 and EOT (Visit 8) • Additional UV1 vaccination (arm B) 3 times the week before initiation of pembrolizumab followed by 5 additional applications on d1 cycle 1-5. • Adverse events • Concomitant medication • Radiological response (according to iRECIST) will be assessed at visit 8 (routine diagnostics)

